**Table 1. Visit Schedule**

| **Procedure***** | **Visit 1**  **(day 1)** | **Visit 2**  **(day 2-8)** | **Visit 3**  **(days 5-14)** | **Visit 4-12**  **(days 2-10)** |
| --- | --- | --- | --- | --- |
| Consent | X |  |  |  |
| Surveys/questionnaires***** | X | X | X | X |
| Fitness test* | X | X | X |  |
| EKG | X |  |  |  |
| Vital Signs | X |  |  |  |
| Exercise**,*** |  | X | X | X |
| fMRI**** | X | X | X |  |
| Urine Tests | X | X | X | X |
| Buccal cells or Saliva (DNA) | X |  |  |  |
| Breath test | X | X | X |  |

*VO2max – assessment of physical fitness. This test will be done during Visit #1, #2, or #3.

** exercise in randomized order. The participant will be asked to run or jog on a treadmill at a speed approximately 20-50% lower than your fast running speed and/or walk at a comfortable speed during Visit #4 – Visit #12.

*** - Participant may be asked to come to one, two, three, four, five, or six visits.

**** - functional magnetic resonance imaging (test to picture parts of brain). This will be done twice, either during Visit #1 and Visit #3 or during Visit # 2 and Visit #3.

*****On the days a subject is not scheduled for a visit, we may ask questions from the Marijuana Craving Questionnaire, Caffeine and Nicotine Use questionnaire, and Drug use (question Page 13 Question 1: Marijuana (as a dried plant) over the phone. The subject will get copies of these questionnaires so they will know questions we may ask them.

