**Mock Scanner Practice Session**

Prior to the fMRI scan day (preferably during the screening visit), screened and consented participants will be given an opportunity to visit the Imaging Institute and participate in a mock scanner session rehearsal to minimize anxiety and novelty effects. Participants will view neutral cues (using a different set of neutral cues than employed on the study day) while lying on a scanner table with audio playback of previously recorded scanner sounds. Participants may repeat the mock scanner rehearsal sessions until they are comfortable with the overall environment. Participants having intolerable anxiety or other difficulties that will likely interfere with successful study participation will be excluded at this point.

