### Visits 2 and 6.

### Exercise.

### Exercise session will be performed during Visits #4 - #10 at random order.

1. Vigorous exercise.

Each participant will be asked to run/jog on the treadmill for up to 30 minutes at the speed that would be about 20-50% lower than the highest speed they were able to run during the treadmill test at Visit #1 or at a speed that is comfortable to the participant.

During the exercise session, heart rate will be monitored.

1. Light exercise.

Each participant will be asked to walk on the treadmill for 30 minutes at their casual walking speed (2.0 -2.5 METs – metabolic equivalents). During the exercise session, heart rate will be monitored.

**Urine Samples** –Participants will be supplied with urine collection cups and asked to collect a spot urine sample at the beginning of each visit before the exercise session starts.

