**Scans**

Scans will be obtained after 30 minute rest following the exercise. We will conduct neuroimaging sessions at times that are convenient for the participants. The combination of weekday and weekend scan options is chosen to optimize participation of participants who may work or be otherwise occupied during weekdays.

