**Stimuli**

Cannabis stimulus

Content: We will use cannabis stimulus as described by Field et al.(Field, Eastwood et al. 2006). It includes pictures of cannabis in different forms and its use (people smoking joints) and related paraphernalia (e.g. bongs, pipes).

Food stimulus.

Content:Existing studies have shown clear brain effects of food cues that activate limbic, cognitive and reward regions. (Holsen et al., 2005). Killgore et al. (2003) have shown that caloric content of the food stimulus employed (i.e. high calorie versus low calorie) produces differential effects on regional brain activation. In this study we will use a stimulus set that includes only high caloric (high energy) food cues versus nature comparisons.

Paradigm:A block trial design is planned based upon our desire to employ a previously successful paradigm (Killgore et al., 2003) and because our goal is to maximize our chances of detecting activation differences (Birn et al., 2002). We will provisionally model our design on that of Killgore et al., 2003 by employing individual scanner runs of food images, cannabis-related images, and nature scenes. To control for non-specific aspects of visual stimulation, we will used blurred Gaussian images (similar to Holsen et al., 2005) as the fixation task. After Killgore et al., (2003) we will present images in 30-second blocks of 10 images each, displayed for 2500 milliseconds with a 500 millisecond interstimulus delay. To minimize the risk of participant motion effects precluding trial analysis, we will keep limit each scanner run to 3 minutes 30 seconds (i.e. 3 target stimulus 30 second blocks, 4 blurred Gaussian background blocks) minutes. The particular food, cannabis, or nature image sequences used will be randomized across scans and the order will be counterbalanced. Participants will have 3 scanner runs of the 3 minute 30 second stimulus display per exercise condition, so that each stimulus set will be seen 3 times/exercise condition. A different set of images will be used for the moderate and vigorous interventions and will be balanced across participants to neutralize order effects.

The total time in the scanner is about 1 hour/day.

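### The Visit 1+3 scan option gives no scan after each exercise condition and confounds exercise with scan order; the exercise text also contradicts Table 1 for the Visit 2+3 option

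*Protocol*

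**What the plan says.** **What the comparison needs.** Three places in the Protocol describe the same design.

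- Study Procedures, Scans: "Scans will be obtained after 30 minute rest following the exercise".
- Study Procedures, Stimuli: "Participants will have 3 scanner runs of the 3 minute 30 second stimulus display per exercise condition". Each condition gets its own image set.
- Statistical Considerations, General statistical methods: the second aim is analysed as within-person change in activation after the two exercise conditions, and the resulting effect sizes are to power the next study.

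**What the schedule provides.**

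- Table 1, fMRI footnote: "This will be done twice, either during Visit #1 and Visit #3 or during Visit # 2 and Visit #3". The fMRI row is marked at Visits 1, 2 and 3 and is blank for Visits 4 to 12.
- Table 1, Exercise row: blank at Visit 1, marked at Visits 2 and 3 and at Visits 4 to 12.
- Table 1, footnote to the Exercise row: participants run or jog and/or "walk at a comfortable speed during Visit #4", continuing to Visit 12.
- Exercise text, under a heading that names Visits 2 and 6: "Exercise session will be performed during Visits #4 - #10 at random order".

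**The concern.** Where and when the conditions and scans take place is for the protocol to fix, and here its parts disagree. Under the Visit 1+3 option the first scan follows no assigned exercise, so the pair cannot compare light with vigorous exercise. The no-exercise scan also always comes first, so any change between a first and a second scan (familiarity with the scanner, habituation to cues) cannot be told apart from an exercise effect.

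The protocol itself takes such changes seriously. Participants may "participate in a mock scanner session rehearsal to minimize anxiety and novelty effects", and the image sets "will be balanced across participants to neutralize order effects". Balancing image sets across participants does not balance exercise against scan order.

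At stake is the within-person effect size. Power Estimates treats effect sizes as a key product of the pilot. If pairs of the none-versus-exercise kind are mixed with light-versus-vigorous pairs, the result estimates neither contrast.

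**Working it through.** The protocol states no figure to reproduce on this point. The check sets the permitted scan pairs against each stated placement of exercise, then writes out what each kind of pair estimates.

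**Step 1. Number of scans that fall on an exercise visit**

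| Stated placement of exercise | Scans at Visits 1+3 | Scans at Visits 2+3 |
| --- | --- | --- |
| Exercise row: Visits 2, 3, 4–12 | 1 of 2 (second scan) | 2 of 2 |
| Footnote to that row, range applied to all exercise: Visits 4–12 | 0 of 2 | 0 of 2 |
| Exercise text: Visits 4–10 | 0 of 2 | 0 of 2 |
| Heading over that text: Visits 2 and 6 | 0 of 2 | 1 of 2 (first scan) |

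Only one cell, Visits 2+3 read with the Exercise row, puts exercise at both scans. No cell in the Visit 1+3 column does, whichever placement is right. The table shows where the text conflicts. It does not measure how often the comparison would fail.

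**Step 2. What each pair estimates**

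Let e(none), e(light) and e(vig) be mean activation under each prior exercise state, and let s be the mean change from first to second scan that is unrelated to exercise. Assume no carry-over from one condition to the next.

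- Visits 1+3, taking exercise to occur at Visit 3: second minus first = [e(exercise) − e(none)] + s, in every participant.
- Visits 2+3, light first: vigorous minus light = [e(vig) − e(light)] + s.
- Visits 2+3, vigorous first: vigorous minus light = [e(vig) − e(light)] − s.

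With the two orders equally represented, the Visit 2+3 mean is ½{[e(vig) − e(light)] + s} + ½{[e(vig) − e(light)] − s} = e(vig) − e(light), so s cancels. In Visit 1+3 pairs s has the same sign for everyone. Averaging over n people leaves it whole, and n does not appear in the expression. Within those pairs exercise state and scan order are the same variable, so a model cannot separate them. Borrowing s from Visit 2+3 pairs would require assuming that it is equal in both groups.

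**Step 3. Whether the day windows allow another design**

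Table 1 gives Visit 1 on day 1, Visit 2 on days 2–8, Visit 3 on days 5–14 and Visits 4–12 on days 2–10.

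- Scans at Visits 1+3: if Visit 3 is on day 5, days 2–4 lie between the scans (3 days). If it is on day 11 or later, days 2–10 do (9 days).
- Scans at Visits 2+3: from 0 days up to 8 (Visit 2 on day 2, Visit 3 on day 11 or later, leaving days 3–10).

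These are calendar days, not sessions held. They show that a baseline scan, a series of exercise sessions and a follow-up scan would fit the calendar, and that extra sessions could fall between two Visit 2+3 scans.

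**The case against.** The best defence is that the intended design can largely be recovered. The Exercise row marks Visits 2 and 3. Study Procedures describes a screening visit followed by a study visit, and the mock session is meant to precede the scan day, preferably at screening. Scans, Stimuli and the analysis section all assume exercise before each scan. This stands in part: a reader might infer that the schedule never delivers the comparison, and that goes too far, because Visits 2+3 read with the Exercise row does deliver it. It does not rescue the Visit 1+3 option, which is stated outright, or the Exercise text.

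Four further inferences are tempting but not supported.

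- *That the Exercise-row footnote cancels the marks at Visits 2 and 3.* Its visit range may attach to the walking alone. Even then, it names no scan visit for the walk.
- *That few sessions can fit between scans.* Table 1 also says: "Participant may be asked to come to one, two, three, four, five, or six visits". Its marker stands on the Exercise row, so it may limit exercise visits rather than all visits. No ceiling on sessions follows.
- *That Visit 1+3 pairs will be analysed as light versus vigorous.* Nothing says so. The planned model includes prior exercise state, which could take the value none. However, the same section speaks only of change after two exercise conditions.
- *That the effect size is biased by some amount.* Neither the scan-order change nor the share of Visit 1+3 participants is given.

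Pilot status softens the consequences but does not remove them, since effect sizes for the next study are a declared output.

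**Conclusion.** The point holds in a limited form. The Visit 1+3 scan option is incompatible with the within-person comparison of two exercise conditions: its first scan has no assigned exercise, and exercise is fully confounded with scan order in every such pair. For the Visit 2+3 option the Exercise row supports the comparison, but the Exercise text and its heading contradict that row, as does the footnote on one reading.

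Any scan-order change carries over one for one into the Visit 1+3 contrast at any sample size; its magnitude is unknown. The conclusion takes Table 1's blank at Visit 1 to mean that no exercise condition is given there, and takes Scans, Stimuli and General statistical methods to describe the intended design. If a before-and-after exercise series was intended instead, the contradiction moves to those three sections and the scan-order confounding remains. The text should be settled before scanning, because the confounding within those pairs cannot be undone afterwards.

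**What to change.** 1. Remove the Visit 1+3 scan option from the fMRI footnote and the Visit 1 mark from the fMRI row.
2. State in Table 1, its footnotes and the Exercise text that light and vigorous exercise are done in randomised order at Visits 2 and 3, each followed by a 30-minute rest and then the scan. Correct the heading over that text.
3. Fix the VO2max test at Visit 1. Table 1 now allows it at Visit 1, 2 or 3, which could put a maximal test on a scan day, while the Exercise text bases the vigorous speed mainly on the Visit 1 treadmill test.
4. Drop the Visit 4–12 sessions, or schedule them so that none falls between the two scans.
5. If any Visit 1+3 scans are kept or already exist, code prior exercise state as none, light or vigorous, and do not pool those pairs as light-versus-vigorous.

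If a baseline, exercise-series, follow-up design was intended, rewrite Scans, Stimuli and General statistical methods to say so, and acknowledge the scan-order confounding.

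The cost is a protocol amendment, less scheduling flexibility, and possibly one more visit for participants who would otherwise have attended only Visits 1 and 3.

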**Visit 1.**

Consent/Screening

After signing an informed consent, participants will be screened for psychiatric conditions using the MINI questionnaire. No included participants will have a lifetime Axis I psychiatric diagnosis other than cannabis or nicotine dependence for cases and nicotine dependence for controls.

Participants will also complete detailed substance abuse questionnaire using a time-line follow back method (Fals-Stewart et al. 2000).  The questionnaires probe drug use history in alcohol, cannabis, stimulants, hallucinogens, opiates, sedatives, dissociative anesthetics, anabolic steroids, and inhalants. The questionnaire contains items to indicate when a specific drug was last used, number of total lifetime episodes, episodes in the last monthand/or last week, whether the participant intended to use the drug in the future, and approximate amount of the drug used ([name] et al. 2006; [name] et al. 2007).

Participants will also complete a Spielberger Strait Trait Questionnaire which is a self-evaluation questionnaire that asks the participant how he or she feels at the moment and in general. They will also fill out a BIS/BAS questionnaire which asks questions about mood, emotions, and behaviors.

Urine pregnancy test – will be screened at each visit to rule out pregnancy (urine; QuPid One Step Pregnancy Test; Stanbio Laboratory, Inc. San Antonio, TX),

Recent drug use will be screened at each visit.

- urine; amphetamines, methamphetamines, barbiturates, benzodiazepines, cannabinoids, cocaine, opiates, PCP and tricyclic antidepressants; Triage Drugs of Abuse Panel, Biosite Diagnostics, San Diego, CA)
- breath - alcohol use (Alco Sensor III, Intoximeters, St. Louis, MO).

**VO2 max testing:** Prior to the test, supine and standing EKG’s will be performed to rule out any rhythmic abnormalities. We had a rough time when some of our normal controls came back with minor abnormalities and we had stated any abnormalities were exclusionary. Participants will be asked to perform a walk/jog test on a treadmill (Bruce Protocol) while oxygen intake and carbon dioxide production are measured.

Participants having a positive urine (other than cannabis for cannabis users), pregnancy, or alcohol screen will be removed from the study prior to MRI scanning.

**Mock Scanner Practice Session**

Prior to the fMRI scan day (preferably during the screening visit), screened and consented participants will be given an opportunity to visit the Imaging Institute and participate in a mock scanner session rehearsal to minimize anxiety and novelty effects. Participants will view neutral cues (using a different set of neutral cues than employed on the study day) while lying on a scanner table with audio playback of previously recorded scanner sounds. Participants may repeat the mock scanner rehearsal sessions until they are comfortable with the overall environment. Participants having intolerable anxiety or other difficulties that will likely interfere with successful study participation will be excluded at this point.

### Fasting

All participants will be asked to avoid the ingestion of any energy (calorie) or caffeine containing food or beverages for 5 hours prior to the study but will be allowed 8 ounces (one cup) of water during these 5 hours.

**DNA sampling** will be done using buccal cells obtained by swabbing the cheek area inside the mouth of the participant or by obtaining a saliva sample.

**Attention and memory testing**

To enhance participants’ attention and memory to displayed images, participants will be asked to remember the presented images and will be told that they will be quizzed on the images immediately after finishing a scan session. Testing will be performed immediately after participant has been removed from the scanner. As described by Killgore et al. (2003) the previously seen images will be mixed with 50% novel distractor images.

### Visits 2 and 6.

### Exercise.

### Exercise session will be performed during Visits #4 - #10 at random order.

1. Vigorous exercise.

Each participant will be asked to run/jog on the treadmill for up to 30 minutes at the speed that would be about 20-50% lower than the highest speed they were able to run during the treadmill test at Visit #1 or at a speed that is comfortable to the participant.

During the exercise session, heart rate will be monitored.

1. Light exercise.

Each participant will be asked to walk on the treadmill for 30 minutes at their casual walking speed (2.0 -2.5 METs – metabolic equivalents). During the exercise session, heart rate will be monitored.

**Urine Samples** –Participants will be supplied with urine collection cups and asked to collect a spot urine sample at the beginning of each visit before the exercise session starts.

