*Physical: -* Magnetic resonance procedures themselves do not utilize ionizing radiation, and there are no common physical risks to MRI procedures. Minor physical discomfort may occur while lying in the scanner.

*Psychological:* – Potential psychological risks include anxiety during various procedures. Some individuals (5-10%) become claustrophobic in the MR scanner, leading to premature termination of the study. Proposed measures to minimize imaging risks -- The Imaging Institute, including [name] group, has extensive experience in MRI research studies with adults. Our staff and imaging center personnel are very experienced in keeping participants comfortable during scanning procedures. Participants are carefully screened for indwelling metal or medical devices that might pose a danger in the scanner. We follow a complete and in-depth screening procedure designed to identify any participant with a mental health disorder that might make him/her particularly vulnerable to these procedures.

Potential Risk of Exercise Testing (VO2max)

To assess physical capability to perform exercise (walking and running), participant will be given a graded-treadmill test using age appropriate protocol. During the test, participant will be closely monitored and will be instructed to stop the test when they choose. The test will be stopped by the research team if their heart rate exceeds their maximum heart rate (220 – age). The test will be preceded with assessment performed by a physician or designated nurse and would include EKG to screen out participants with abnormal EKG response from the treadmill test.

The criteria include:

- ST-segment depression (defined as ≥1.0 mm of horizontal or down-sloping ST at 80 msec beyond the J point, suggesting myocardial ischemia)
- Ventricular arrhythmias, presenting as frequent multiform PVC, and especially in combination with ST depressions
- Heart rate response that >2 standard deviations (>20 beats/min) below the age-predicted maximal HR who are limited by volitional fatigue
- A change in Diastolic blood pressure >15 mmHg
- Anginal symptoms > 2 (out of 1-4 scale, corresponding to chest pains of perceptible but mild, moderate, moderately severe, and severe intensities, respectively).

Potential Risk of Exercise.

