There is potential risk of injury caused by walking or jogging on the treadmill. The common symptoms include shortness of breath, or more severe, such as falling down. Also, there may be the rare instance of heart problems, such as a heart attack, that could be life threatening. We will do a fitness test to screen if each participant is capable to walk or run for 20 to 30 minutes.

Potential Risks of Genotyping.

There is a very low risk that genotyping information may be disclosed and participant could suffer potential embarrassment or economic harm.

Potential Social/Legal Risks.

There are potential social risks to participants if the confidentiality of the information they provide us is disclosed. For this reason, we follow strict confidentiality procedures.

1. **Reporting of Adverse Events or Unanticipated Problems involving Risk to Participants or Others**

An adverse event (AE) is any untoward medical occurrence in a participant, not necessarily having a causal relationship with the study. A serious adverse event (SAE) is any untoward medical occurrence that a) results in death, b) is life-threatening, c) requires inpatient hospitalization or prolongation of existing hospitalization, d) results in persistent or significant disability/incapacity, or e) is a congenital anomaly/birth defect.

AE’s are graded as:

- Mild (no limitation of usual activities)
- Moderate (some limitation)
- Severe (inability to carry out usual activities)

AE’s are attributed according to the relationship to the study procedures as:

- Not related
- Unlikely
- Possible
- Probable
- Definite

SAE’s are reported immediately by telephone to the VU IRB. Adverse events will be detected by clinical examinations by the studies clinical investigator. An Adverse Event Report form will be completed and returned to the VU IRB within 5 working days. Summary Reports are submitted to the VU IRB and will contain a) The number of adverse events and an explanation of how each event was handled, b) The number of complaints and how each complaint was handled, c) The number of participant withdrawals and an explanation of why the participant withdrew or was withdrawn, and d) The number of protocol violations and how each was handled.

1. **Study Withdrawal/Discontinuation**

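### The vigorous session may be run at any comfortable speed with no minimum duration, and Table 1 lets the treadmill test that sets its speed come after exercise has begun, so the Aim 2 effect size would rest on an undefined dose.

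*Protocol*

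**What the plan says.** **Dose.** The Exercise section of the Protocol (under Visits 2 and 6) asks participants in the vigorous condition to "run/jog on the treadmill for up to 30 minutes". The speed is to be about 20% to 50% below the highest speed run in the treadmill test at Visit 1, "or at a speed that is comfortable to the participant". On intensity it adds only "During the exercise session, heart rate will be monitored", with no target. The light condition in the same section is a 30-minute walk at 2.0-2.5 METs.

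The exercise footnote to Table 1 words it differently: "at a speed approximately 20-50% lower than your fast running speed and/or walk at a comfortable speed". There, comfort governs the walk and not the run.

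**Timing of the test.** The Visit 1 section describes VO2max testing as part of that visit, and the Exercise section also takes the speed from Visit 1. The VO2max footnote to Table 1 says otherwise: "This test will be done during Visit #1, #2, or #3". Table 1 marks exercise at Visit 2, Visit 3 and Visits 4-12.

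**Role of the test.** The Risks section gives it a screening purpose. The assessment around it "would include EKG to screen out participants with abnormal EKG response from the treadmill test". On the exercise sessions it says: "We will do a fitness test to screen if each participant is capable to walk or run for 20 to 30 minutes".

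**Use of the result.** The Specific Aims include the effect of vigorous exercise on brain activation and craving. General statistical methods says the Aim 2 effect sizes will power the planned R01, and Power Estimates calls effect sizes a key outcome.

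**The concern.** A pilot whose main product is an effect size has to say what the effect is an effect of. Here the comparator has a set duration and intensity, while the condition named in the aim has an upper time limit and a speed that the participant may choose. If the estimate is small, the reader cannot tell whether vigorous exercise does little or whether little vigorous exercise was delivered. If it is large, a later study has no stated dose to reproduce.

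The scheduling conflict adds to this. A participant who exercises before the treadmill test has no top test speed from which to take 20% to 50%, so the comfort option is the only rule left. The same participant starts exercise without the capability check and the exercise EKG response that the Risks section relies on.

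The secondary hypothesis compares users with controls. The groups are matched approximately on gender, age, height and education, not on fitness. If they chose different comfortable speeds, dose would differ by group. The Protocol does not say that this will happen, but it does not prevent it and, apart from heart rate, does not provide for it to be seen.

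**Working it through.** The Protocol has no calculated figure that depends on this point: 10 per group is justified as usual for fMRI pilots, without an effect size. The check is therefore mainly a comparison of texts, with a little arithmetic on the dose range.

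**1. Is the percentage rule binding?** The Exercise section joins the rule and the comfortable speed with an or. Any comfortable running speed satisfies the instruction, so the rule is optional.

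**2. Is there a minimum duration?** The session text gives only a ceiling of 30 minutes. The 20 to 30 minutes in the Risks section describes what the participant must be capable of, not what a session must contain.

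**3. How wide is the rule by itself?** Speeds 20% to 50% below the top are 80% to 50% of it. Ratio: 0.80 / 0.50 = 1.6.

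**4. With duration, as an illustration.** Assume sessions of 20 to 30 minutes, borrowing the capability range. Distance in units of top-speed minutes:
- lowest: 0.50 × 20 = 10
- highest: 0.80 × 30 = 24
- ratio: 24 / 10 = 2.4

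This excludes the comfort option. The 20-minute lower end is an assumption, since the Protocol sets none.

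**5. Can exercise precede the test?** Table 1 gives these windows:

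| Visit | Days | Exercise marked | Fitness test marked |
|---|---|---|---|
| 1 | 1 | no | yes |
| 2 | 2-8 | yes | yes |
| 3 | 5-14 | yes | yes |
| 4-12 | 2-10 | yes | no |

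With the test at Visit 3, an exercise session at Visit 2 precedes it by visit order. A session at one of Visits 4-12 can precede it by date: exercise on day 2 and the test on day 5 are 5 − 2 = 3 days apart, and the windows allow up to 14 − 2 = 12 days. With the test at Visit 2 on day 8, a Visit 4-12 session on day 2 also comes first. Higher visit numbers therefore do not mean later dates.

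**6. Do other sections settle it?** The Visit 1 and Exercise sections point to a test at Visit 1. The table footnote contradicts them, and nothing says which prevails.

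**The case against.** The best answer is that the intent is clear and the study is a feasibility pilot.

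- **Run/jog is itself a floor.** The comfort wording changes the speed of a run; it does not turn the session into a walk. This stands. A reader might infer that vigorous sessions could match the light walk, or work out how far a later sample size would inflate if some sessions gave no contrast. The Protocol gives no basis for any such share, and the run/jog instruction against 2.0-2.5 METs speaks against it.
- **The test is meant to come first.** The Exercise section puts exercise at Visits 4-10, and the Table 1 footnote speaks of Visits 4-12, all numbered after the visits where the test may fall. This shows intent, but it does not close the gap: those visits fall on days 2-10, Visit 3 on days 5-14, and the table also marks exercise at Visits 2 and 3.
- **Safety screening is not lost.** Table 1 has an EKG and vital signs at Visit 1 whenever the treadmill test is done. This stands. A reader might infer that participants could exercise with no EKG at all, and the table does not support that. What can come late is the exercise response and the capability check.
- **Heart rate is monitored.** This helps describe intensity afterwards, but there is no target to judge it against, and the session text does not call for recording speed or minutes.
- **Self-pacing is legitimate in a pilot.** It is, and the estimate would still describe a self-paced instruction. The aim, however, names vigorous exercise, and the Protocol does not present self-pacing as the condition under study.

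**Conclusion.** The point holds as a matter of clarity and interpretation, and is worth a small amendment. Two facts come straight from the text: the comfort option makes the percentage rule optional with no minimum time, and Table 1 permits the treadmill test after exercise has begun, in conflict with the Visit 1 and Exercise sections.

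The size is only partly known. The percentage rule spans 1.6-fold in speed. The 2.4-fold figure holds only if sessions last 20 to 30 minutes. How often sessions would be slow, short or ahead of the test is not known, and neither is any effect on the Aim 2 estimate. A reader might go further and conclude that Aim 2 is biased or that the exercise contrast is lost. The documents do not support either: the run/jog versus walk contrast remains, and no figure in the Protocol changes. What is affected is how far the effect size can be carried into later research.

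**What to change.** 1. **Table 1, VO2max footnote:** require the treadmill test at Visit 1, or in any case before the first exercise session, in line with the Visit 1 and Exercise sections.
2. **Exercise section, vigorous condition:** make 20% to 50% below top test speed the default, with a 30-minute target. Replace the free choice of a comfortable speed with permission to slow or stop only for safety or intolerance. Align the exercise footnote to Table 1 with this.
3. **Recording:** for each session, record achieved heart rate, speed and minutes, and summarise them by condition and group.
4. **Analysis:** keep every session in the condition to which it was randomised, including sessions that were slowed or cut short.

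A minimum heart rate could be added, but in a self-paced pilot that is for the investigators to decide. Some variation in dose will remain, since the default band is still 1.6-fold wide and slowing is allowed, but it will be documented.

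The cost is slightly less flexibility in scheduling the test and in pacing, and a little more recording.
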